**3.5 Statistical Analysis**

Descriptive statistics will be used for demographic variables such as age, weight, height and BMI. Data of plasma hormones will be evaluated by area and plasma concentration time curves (AUC) and maximum plasma concentrations (Cmax) assessed by linear regression analysis. All statistical analysis will be done using SPSS for windows software (version 22.0). Values will be reported as mean ± SEM. Differences will be considered as significant when P ≤ 0.05.

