**2. Objective**

The aim of this study is to examine the effect of different concentrations of glucose on the release of gastrointestinal satiation peptides (PYY, GLP-1, GIP and ghrelin), as well as on plasma insulin, c-peptide, glucose and glucagon levels in healthy normal weight and obese humans. In addition we examine the gastric emptying rates of these different glucose loads.

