**Experimental procedure**

Subjects will be admitted to the Phase 1 Research Unit of the University Basel in the morning after fasting overnight for at least 10 hours. An antecubital vein catheter will be inserted for blood drawing and a gastric tube will be swallowed. Fasting and postprandial blood samples will be taken from all participants. After taking the fasting samples (-10, -1 min), each patient will receive 300 mL of a test solution (tap water) that contains either 10 g glucose, 25 g glucose, 75 g glucose or nothing (placebo control) (Table 1). Each test solution is labeled with 50 mg ^13^C-sodium acetate for determination of gastric emptying rate. Blood will be drawn at the following time points: 15, 30, 45, 60, 90, 120, and 180 min. A 10 mL samples will be taken at each time point into tubes containing EDTA (6 µmol/l), a protease inhibitor cocktail (Complete^®^, EDTA-free, 1 tablet/50 ml blood; Roche, Mannheim, Germany) and a dipeptidylpeptidase IV inhibitor (10 μl/ml; Millipore Corporation, St. Charles, Missouri, USA). The total blood volume taken during one test day will be 100 mL. After centrifugation, plasma samples will be kept frozen at -20°C until analysis. Glucose and the following peptides will be measured: insulin, c-peptide, glucagon, PYY, GLP-1, GIP and ghrelin. For the determination of the gastric emptying rate, breath samples will be taken at -1, 15, 30, 45, 60, 75, 90, 105, 120, 150, 180, 210 and 240 min after intake of the test solution. Breath samples will be collected in foil bags.

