**3.3 Assessment of gastric emptying**

Gastric emptying rates will be assessed using the ^13^C-sodium acetate breath test. This test is an accurate, non-invasive, simple method without radiation exposure, and represents a reliable alternative to scintigraphy, the gold standard for measuring gastric emptying (1, 2). The test solutions will be labelled with 50 mg ^13^C-sodium acetate; the substrate is rapidly absorbed in the proximal small intestine, metabolized in the liver with the production of ^13^CO_2_ which is exhaled rapidly, thus, reflecting gastric emptying of nutrients (1, 2). Subjects will be asked to exhale through a mouth-piece to collect an end-expiratory breath sample into a 100 mL foil bag at certain time intervals. The ^13^CO_2_ breath content will be determined by non-dispersive infrared spectroscopy using an isotope ratio mass spectrophotometer (IRIS; Wagner Analysen Technik, Bremen, Germany). ^13^C-abundance in breath is expressed as relative difference (δ ‰) from the universal reference standard (carbon from Pee Dee Belemnite limestone). ^13^C-enrichment is defined as the difference between preprandial ^13^C-abundance in breath and ^13^C-abundance at the defined time points postprandially and is given in δ over basal (DOB, ‰). Based on these values, time to reach maximal emptying speed and areas under the curve of the responses will be calculated (2, 3).

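### Hormone AUC and Cmax are not referred to the fasting samples, so comparisons of obese with normal-weight subjects would mix fasting level with response, and comparisons of loads may lose precision

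*Protocol*

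**What the plan says.** The objective in section 2 is "to examine the effect of different concentrations of glucose on the release of gastrointestinal satiation peptides", in normal-weight and obese subjects.

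Section 3.2 (Experimental procedure) provides two fasting blood samples on every test day: "After taking the fasting samples (-10, -1 min), each patient will receive 300 mL of a test solution". The later draws are also fixed: "Blood will be drawn at the following time points: 15, 30, 45, 60, 90, 120, and 180 min".

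Section 3.5 gives the hormone measures. The first is an area: "Data of plasma hormones will be evaluated by area and plasma concentration time curves (AUC" (the protocol's own wording). The second is "maximum plasma concentrations (Cmax) assessed by linear regression analysis". The section mentions no baseline, increment, change from fasting or fasting covariate.

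For the breath test, section 3.3 defines enrichment as the difference from the preprandial value, which "is given in δ over basal (DOB", and bases the areas on those values.

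**The concern.** Release after a glucose load is a change from the fasting state. A maximum concentration, as worded, is an absolute level. The area under a concentration-time curve with no qualifier would ordinarily be taken as the total area. Both contain the fasting level. Over three hours the fasting level can make up most of the total area, above all on the water day and after the 10 g and 25 g loads.

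Two things are at stake, and they differ in kind:

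- **Between weight groups: bias.** Weight group is not randomised. A fasting difference between obese and normal-weight subjects would appear as a difference in response.
- **Between loads: precision.** Each subject receives all four solutions in random order. Day-to-day fasting variation is therefore noise, but it can hide the small responses to the low loads, whose effect in these subjects section 1 describes as unknown.

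**Working it through.** The protocol gives no fasting level, SD, effect size or power, so there is no figure of its own to reproduce. The inputs it does give are the sampling times (section 3.2), 12 subjects per group (section 3.1), P ≤ 0.05 (section 3.5; two-sided assumed), and an intra-assay CV below 9.5% for GLP-1, GIP and PYY (section 3.4). Everything else below is assumed. AUC is taken by the trapezoid rule from intake to 180 min, with the mean of the two fasting samples as the time-0 value in step 3.

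**1. Weight of the fasting level.** The trapezoid weights at 0, 15, 30, 45, 60, 90, 120 and 180 min are 7.5, 15, 15, 15, 22.5, 30, 45 and 30, which sum to 180. One unit of fasting difference therefore adds 1 × 180 = 180 unit x min to total AUC. For an equal rise it adds about 1 unit to Cmax.

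**2. Group comparison, identical true response.** Assumptions: fasting mean 5 units, between-subject SD 1, day-to-day SD 0.5, peak rise 5 (SD 1), noise SD 0.3, 12 versus 12, t-test. A rise of unit height has area 74.25 in the assumed shape (0, 0.6, 1, 0.9, 0.7, 0.4, 0.2, 0 at the eight times). Rate of P ≤ 0.05 in 3,000 simulated trials:

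| Fasting gap (units) | Added to AUC | Total AUC | Raw Cmax |
|---|---|---|---|
| 0 | 0 | 0.06 | 0.05 |
| 0.5 | 90 | 0.16 | 0.11 |
| 1 | 180 | 0.51 | 0.34 |
| 2 | 360 | 0.98 | 0.87 |

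Minus the fasting mean, both measures stay between 0.045 and 0.053 at every gap.

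**3. Load versus water, within subject.** Assumptions: fasting level scaled to 1, a rise peaking at 15 min at 50% of fasting and gone by 45 min, sample CV s = 9.5%, and day-to-day fasting CV c. The true difference in AUC is 0.5 × 15 × (1 + 0.5) = 11.25. Ignoring the small extra noise from the rise, the squared weights of the seven later samples sum to 5006.25, so the SD of the paired difference is:

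- total AUC: √{2[180²c² + s²(7.5²/2 + 5006.25)]} = √{2[32,400c² + 45.4]}
- incremental AUC: √{2s²(172.5²/2 + 5006.25)} = √{2 × 179.5} = 18.9, whatever c is

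At c = 15% the first is √{2(729 + 45.4)} = 39.4. The two are equal when c² = (179.5 − 45.4)/32,400, so c ≈ 6.4%.

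Power (12 subjects, 20,000 simulated trials; the adjusted column regresses the difference in AUC on the difference in baseline):

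| Day-to-day CV | Total AUC | Incremental AUC | Baseline-adjusted AUC |
|---|---|---|---|
| 0% | 95% | 47% | 93% |
| 5% | 61% | 47% | 69% |
| 7% | 42% | 47% | 59% |
| 10% | 26% | 46% | 52% |
| 15% | 15% | 46% | 47% |
| 20% | 11% | 45% | 44% |

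**4. Bias between loads.** In a separate run with two loads of equal effect and the step 2 units, total AUC rejected in about 5% of trials at day-to-day SDs of 0.5 and 1. Its standard error was about 38 and 73, against about 17 for incremental AUC.

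**The case against.** The strongest reply is that section 3.5 is silent rather than wrong. It does not say total, absolute or uncorrected. Incremental AUC, or a fasting covariate in the named regression, would fit the wording for AUC, and a statistical analysis plan that is not shown may specify one. This stands. A reader might infer that the protocol has chosen absolute AUC; the text does not support that. Only Cmax is absolute by its wording.

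A reader might also infer that fasting differences between days are counted as response to glucose. That does not hold as a claim of bias: the loads are randomised within subject, and step 4 shows the error rate is kept.

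Section 3.5 also names no test of obese against normal-weight subjects, and the objective could be met by separate analyses within each group. Load minus water removes a stable fasting gap even from total AUC. Both points stand, so the bias arises only if the groups are compared on uncorrected measures without the water day as reference.

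The power gain rests on assumed values. Below roughly 6 to 7% day-to-day CV, plain incremental AUC is worse than total AUC, because it subtracts 180 times a noisy two-sample mean. With a longer rise (peak at 30 min, gone by 180 min) and 10% CV, power is 95% for total and 100% for incremental AUC, so little is lost. The 9.5% is an upper limit for the intra-assay CV, used here as the sample CV. Finally, total AUC is a legitimate measure of exposure. What remains is that the stated aim is release, and that section 3.3 shows baseline correction being written down for one outcome and not for the other.

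**Conclusion.** The point holds as a gap in definition. The protocol collects a baseline on each test day and does not connect it to the hormone measures on which its aim rests.

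The weight of 180 unit x min per unit of fasting difference follows from the sampling window alone. The false-positive rates of 51% (AUC) and 34% (Cmax), at a gap of one between-subject SD, rest on the assumed SDs and on a direct group comparison of uncorrected values.

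For contrasts between loads the issue is precision only, and its size is uncertain. In the scenario examined, baseline adjustment beats total AUC at every day-to-day CV from 5% to 20%, and over that range it beats incremental AUC or comes within about one percentage point of it. It is slightly worse than total AUC only at 0% (93% versus 95%).

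**What to change.** Amend section 3.5 to state that:

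- baseline is the mean of that day's -10 and -1 min samples;
- comparisons between loads use a within-subject regression of AUC and Cmax on load, with the day-specific baseline as covariate;
- comparisons between weight groups use net incremental AUC over 0 to 180 min and change from baseline to peak, or load minus water;
- the fasting difference between groups is reported separately, as a result in its own right.

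The covariate is preferred for load contrasts because it estimates the slope on baseline instead of forcing it to 180, which avoids the loss of power at low day-to-day CV.

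The cost is wording and one degree of freedom for the covariate. The fasting samples are already planned, so no visit or blood draw is added.

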**3. Methods**

**3.1 Study subjects**

12 healthy normal weight and 12 healthy obese subjects will be recruited. The screening procedure will include the following assessments: a medical interview and a full physical examination. Anthropometric measurements including weight, height, BMI, as well as heart rate and blood pressure will be recorded for all participants.

The following inclusion criteria are applied:

- Healthy normal weight subjects with a body-mass index of 19.0-24.5 or healthy obese subjects with a body-mass index of > 30
- Normal eating habits
- Age 18-40 years
- Stable body weight for at least three months

Exclusion criteria:

- Smoking
- Substance abuse
- Regular intake of medications (except for oral contraceptives)
- Medical or psychiatric illness
- Any abnormality detected during the screening procedure
- history of gastrointestinal disorders
- food allergies

The protocol will be submitted and approved by the Human Ethical Research Committee of the University of Basel. All subjects will have to give written informed consent.

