**3.2 Study protocol**

**Overall design**

The study will be performed as a randomized, placebo-controlled, four-way crossover study, with each subject studied on four test days at least three days apart. The test trials will be identical in design except for the administered test solution (Figure 1).

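### Linear regression is the only inferential method named for a four-period crossover, with no provision for the four correlated test days per subject

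*Protocol*

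**What the plan says.** The Overall design paragraph of section 3.2 sets a "randomized, placebo-controlled, four-way crossover study, with each subject studied on four test days at least three days apart". The four test solutions contain 0, 10, 25 or 75 g of glucose. Section 3.1 states that "12 healthy normal weight and 12 healthy obese subjects will be recruited". Section 2 asks how the different glucose concentrations affect satiation peptides and "plasma insulin, c-peptide, glucose and glucagon levels in healthy normal weight and obese humans".

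Section 3.5 holds the whole statistical method. Hormone data are summarised as AUC and "maximum plasma concentrations (Cmax) assessed by linear regression analysis", in SPSS version 22, and "Differences will be considered as significant when P ≤ 0.05". No model term of any kind is listed: not load, weight group, subject or period. The section gives no standard deviation, within-subject correlation, effect size or power target.

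**The concern.** Linear regression in its ordinary meaning assumes independent observations. Here each subject contributes four values of every response, and those values will be correlated because people differ in their general level of insulin, GLP-1 and so on. A crossover is chosen so that this between-subject variation cancels from the comparison of loads. A model without a subject term puts it back into the error.

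The two kinds of comparison then go wrong in opposite directions. For load against water, the standard error is too large. The 10 g and 25 g contrasts bear on the question raised in the Introduction, and they are the ones most plausibly small, so that is where lost power would matter. For a comparison of weight groups pooled over loads, four days from one person count as four people, the standard error is too small, and false differences are declared too often.

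**Working it through.** The protocol has no sample-size or power figure to reproduce, so the check asks what the named method would do to this design if run as ordinary regression on all subject-days.

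**Inputs from the protocol.** 24 subjects (12 + 12), four loads each, hence 24 × 4 = 96 rows per response; alpha 0.05 (section 3.5).

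**Assumptions.** Two-sided tests; equal variance σ² on each day; a common within-subject correlation ρ, shown at 0.3, 0.5 and 0.7; no period effect.

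**Load-versus-water contrast within one weight group (n = 12).**
- Variance assumed by ordinary regression: 2σ²/n.
- True variance, since both values come from the same subjects: 2σ²(1 − ρ)/n.
- The standard error is therefore overstated by k = 1/√(1 − ρ).
- A within-subject analysis of 12 subjects and four loads has 11 × 3 = 33 error df and critical t = 2.035. Power of 80% corresponds to a noncentrality of 2.886. Holding that effect fixed and raising the critical value to 2.035 × k gives the power of the ordinary regression.

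**Weight-group effect pooled over loads.**
- Variance assumed by ordinary regression, with 48 rows per group taken as independent: 2σ²/48.
- True variance, from 12 subject means per group: (2/12) × σ²(1 + 3ρ)/4 = 2σ²(1 + 3ρ)/48.
- The standard error is therefore understated by m = √(1 + 3ρ).
- True type I error = 2 × P(t with 94 df > 1.986/m).

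| ρ (assumed) | k | 2.035 × k | Power for load vs water (80% if within-subject) | m | 1.986/m | True type I error, pooled group effect |
|---|---|---|---|---|---|---|
| 0.3 | 1.20 | 2.43 | 68% | 1.38 | 1.44 | 15% |
| 0.5 | 1.41 | 2.88 | 51% | 1.58 | 1.26 | 21% |
| 0.7 | 1.83 | 3.71 | 23% | 1.76 | 1.13 | 26% |

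**Simulation check.** 20,000 runs per setting, 24 subjects, a random subject intercept, and regression on load and group without a subject term. At the same three correlations:
- Power was 69%, 53% and 25% where the within-subject contrast had 80%.
- True type I error of the load contrast was 1.9%, 0.8% and 0.1%, so that test is conservative.
- True type I error of the pooled group effect was 15.3%, 22.2% and 27.2%.
- With a subject term for the load contrast, or subject means for the group test, type I error returned to about 5% in both.

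**Dependence on effect size (same simulation, all 24 subjects).** At an effect of 0.5 total SD, power was 38% without a subject term against 67% with one at ρ = 0.5, and 36% against 88% at ρ = 0.7. At 1 SD and ρ = 0.5 it was 98% against 99.8%. At 1.5 SD or more it was about 100% both ways.

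**The case against.** The strongest reply is that section 3.5 is silent rather than wrong. It does not say the regression is ordinary least squares and it rules out no term. It does not list load or group either, so the list of terms is plainly incomplete. A linear regression can carry subject indicators, SPSS fits mixed models, and model terms are often left to an SAP, which is not at hand. The sentence is also loosely built, so that the regression may attach to Cmax alone or to both summaries. This stands to the extent that one cannot say the protocol prescribes a model without subject or period terms; a reader might infer that, but the text does not support it. It does not dispose of the point. The protocol has already named a model class, that class in its usual sense does not fit the crossover, and an SAP with a mixed model would have to reinterpret it.

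Second, no obese-versus-normal-weight test is specified. Section 2 asks about load effects in both kinds of subject, and section 3.5 names no group comparison. That is correct. The inflated type I error belongs to a group effect pooled over loads. If the groups are compared at each load separately, with one row per subject, it does not arise.

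Third, the size of the power loss depends on quantities the protocol does not give, and for the stated aim the error is conservative. Both are true.

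**Conclusion.** The point holds in a conditional form. Section 3.5 names a method that, taken at its ordinary meaning, treats 96 correlated subject-days as independent, and it makes no provision for the repeated measures. Run that way, load-versus-water contrasts lose power, from 80% to about 68%, 51% and 23% at assumed correlations of 0.3, 0.5 and 0.7. A weight-group effect pooled over loads would have a true type I error of about 15%, 21% and 26% at the same correlations.

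Two stronger readings should not be drawn. A reader might infer that the load contrasts lose most of their power. That follows only from a correlation of about 0.6 upwards with small to moderate effects; at 0.5 the loss is about a third of 80%, and for effects of 1.5 total SD or more it is negligible. A reader might also blame the missing period term. All the figures come from omitting the subject term. Period belongs in the model as standard for the design, but no harm from leaving it out has been shown.

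The directions of error are certain for any positive correlation, given ordinary regression on all rows. The sizes rest on the assumed correlation and effect size.

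**What to change.** In section 3.5, replace the reference to linear regression with a linear mixed model for each response (AUC and Cmax of each analyte): a random subject intercept; fixed effects for load (four levels), period, weight group and group by load; and Satterthwaite degrees of freedom. Report the load-versus-water contrasts within each weight group and the group-by-load contrasts. The MIXED procedure in SPSS 22, the software already named, fits this model. The cost is one sentence in the protocol, with no new data and no change to study conduct. If an SAP already specifies such a model, the sentence in section 3.5 should be brought into line with it.

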**4. Materials**

Glucosum anhydricum will be purchased at Hänseler AG, Herisau, Switzerland.

^13^C-Sodium Acetate will be purchased at ReseaChem GmbH, Burgdorf, Switzerland.

